# Sequential dual-site High-Definition transcranial Direct Current Stimulation (HD-tDCS) treatment in chronic subjective tinnitus: study protocol of a double-blind, randomized, placebo-controlled trial

**DOI:** 10.1186/s13063-019-3594-y

**Published:** 2019-08-01

**Keywords:** Chronic tinnitus, Transcranial direct current stimulation, Neuromodulation, Randomized controlled trial

## Abstract

**Background:**

Chronic tinnitus is a highly prevalent symptom, with many patients reporting considerable effects of tinnitus on quality of life. No clear evidence-based treatment options are currently available. While counseling-based methods are valuable in some cases, they are not sufficiently effective for all tinnitus patients. Neuromodulation techniques such as high-definition transcranial direct current stimulation (HD-tDCS) are proposed to have positive effects on tinnitus severity but, to date, these effects have not been proven conclusively. The proposed trial will investigate the hypothesis that chronic tinnitus patients receiving HD-tDCS will report a positive effect on the impact of tinnitus on daily life, as compared to patients receiving sham stimulation.

**Methods:**

This study proposes a randomized, double-blind, placebo-controlled trial with parallel group design. A total of 100 chronic tinnitus patients will be randomly allocated to an experimental group or a sham group, with allocation stratified according to gender and tinnitus severity. Patient and researcher will be blinded to the patient’s allocation. Patients will undergo six sessions of sequential dual-site HD-tDCS of the left temporal area and the right dorsolateral prefrontal cortex. Evaluations will take place at baseline, immediately following treatment, and at three and six months after the start of the therapy. The primary outcome measure is the change in Tinnitus Functional Index (TFI) score. Secondary outcome measures include audiological measurements, cortical auditory evoked potentials, the Repeatable Battery for the Assessment of Neuropsychological Status adjusted for hearing-impaired individuals (RBANS-H), and supplementary questionnaires probing tinnitus severity and additional symptoms. By use of a linear regression model, the effects of HD-tDCS compared to sham stimulation will be assessed.

**Discussion:**

The objective of this study is to evaluate whether HD-tDCS can reduce the impact of tinnitus on daily life in chronic tinnitus patients. To date, published trials on the effects of HD-tDCS on tinnitus suffer from a lack of standardization and few randomized controlled trials exist. The proposed study will be the first adequately powered trial to investigate the effects of sequential dual-site HD-tDCS on tinnitus severity.

**Trial registration:**

ClinicalTrials.gov, NCT03754127. Registered on 22 November 2018.

**Electronic supplementary material:**

The online version of this article (10.1186/s13063-019-3594-y) contains supplementary material, which is available to authorized users.

## Background

Subjective tinnitus is commonly defined as the perception of sound in the absence of a corresponding external sound source. Approximately 10–20% of the population experience tinnitus [1, 2]. A segment of this patient group, amounting to 2–3% of the total adult population, describes their tinnitus as bothersome and interfering with everyday life [3]. Subjective tinnitus is often accompanied by non-specific symptoms such as annoyance, irritability, anxiety, depression, hearing problems, hyperacusis, insomnia, and concentration difficulties [4–6]. For some patients, tinnitus presents a severe burden that considerably affects quality of life. Due, in part, to considerable heterogeneity of the tinnitus patient population, no efficient evidence-based treatment option is currently available and personalized tinnitus therapy is essential [7]. In a specific subgroup of patients for whom tinnitus is accompanied by hearing impairment or single-sided deafness, hearing aids or cochlear implants are beneficial [8, 9]. Although counseling-based methods are proven to be effective for a large subgroup of patients, they sometimes only have modest effects on tinnitus severity and do not affect the underlying pathology [10, 11].

Tinnitus often develops as a result of damage to the cochlea [12]. Possible causes of this cochlear damage include sudden hearing loss, noise trauma, presbyacusis, and infections. However, hearing loss is not a prerequisite for the development of tinnitus and tinnitus perception seems to be regulated mainly by the central nervous system. Cochlear damage may lead to deafferentiation of auditory pathways and maladaptive plastic changes in wide brain networks comprising both cortical and subcortical areas [13]. Thus, tinnitus can be defined as an emergent property of multiple networks activated in parallel [14], with increased spontaneous activity and synchrony of affected neurons leading to its perception [15]. These alterations in brain activity might also be reflected in the cognitive deficits often observed in tinnitus patients [16]. Explorative research into these aspects of tinnitus, using auditory evoked potentials and cognitive tests that are adequately altered for hearing impaired individuals, might lead to a better characterization of different tinnitus subtypes [4, 17, 18].

Neuronal network activity can be modified by neuromodulation techniques such as transcranial direct current stimulation (tDCS). tDCS is a non-invasive and safe experimental therapy whereby the brain is stimulated with externally applied direct current electric fields in order to modify corticospinal excitability [19]. Effects of tDCS transcend the level of individual neurons, as the technique can influence brain-wide functional connectivity, network synchronization, and oscillatory activity [20]. Recently, the development of high-definition tDCS (HD-tDCS) has enabled researchers to stimulate brain regions with increased focality by using a higher number of smaller electrodes [21, 22]. Clinical applications of tDCS and HD-tDCS include pain relief, especially in fibromyalgia, the treatment of major depressive disorder, and tinnitus [23].

In tinnitus treatment, tDCS and HD-tDCS are mainly applied to two target regions: the left temporal area (LTA) and the right dorsolateral prefrontal cortex (rDLPFC) [24]. The LTA comprises the left auditory cortex, which shows hyperactivation in tinnitus patients [25]. The rDLPFC is involved in the integration of sensory and emotional aspects of tinnitus and is an essential part of the tinnitus distress network [26]. Overall, beneficial effects of tDCS of the rDLPFC have been reported and there are some indications of the benefit of tDCS of the LTA, but randomized controlled trials (RCT) on the effects of tDCS on tinnitus are severely lacking (for review, see [27]). In two recent studies reporting the efficacy of (HD-)tDCS of LTA and rDLPFC in tinnitus treatment, no difference in efficacy was found between the two target regions [24, 28]. Current evidence is too weak to make conclusive recommendations on the use of (HD-)tDCS in tinnitus treatment [23]. As such, there is a need for adequately powered double-blind randomized sham-controlled trials.

This study proposes a RCT with parallel group design, in which participants are randomly allocated to the experimental group or the sham group in a 1:1 ratio. This trial intends to investigate the superiority of HD-tDCS treatment over sham stimulation. It is hypothesized that tinnitus patients receiving six consecutive sessions of sequential dual-site HD-tDCS will report a positive effect on the impact of tinnitus on daily life, as compared to tinnitus patients receiving sham stimulation.

## Methods

### Study setting

Patients will be recruited at the tertiary tinnitus clinic of the Antwerp University Hospital (UZA). When tinnitus patients present themselves at the ear-nose-throat department, a thorough diagnostic evaluation takes place. A systematic medical history is obtained and coexistent symptoms (e.g. hearing loss, sleeping disorders, cervical tension or pain, or temporomandibular joint dysfunction) are enquired. Apart from the medical history, psychoacoustic characteristics of the tinnitus sound are quantified and the impact of tinnitus on quality of life is estimated via questionnaires. A thorough clinical exam containing micro-otoscopy, pure-tone audiometry, and psychoacoustic measures is performed. Together, these examinations will allow the evaluator to determine whether the patient meets the inclusion criteria for the study (Table 1). In case inclusion criteria are met, patients will be informed about the clinical trial and asked to participate.

**Table 1 Tab1:** Inclusion and exclusion criteria

Inclusion	Exclusion
- Chronic (> 6 months) subjective tinnitus	- Somatic tinnitus
- 24 < TFI score < 90	- Pregnancy
- Hospital Anxiety and Depression Scale:	- Active middle ear pathology
• Depression subscale < 12	- Hearing implants
• Anxiety subscale < 12	- Known tumors in the head/neck region
- HQ score < 40	- Patient having already had any other tinnitus treatment within the last two months

*TFI* Tinnitus Functional Index, *HADS* Hospital Anxiety and Depression Scale, *HQ* Hyperacusis Questionnaire

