### Eligibility criteria

Adult patients (male/female) with chronic (> 6 months), non-pulsatile subjective tinnitus will be included in the study (Table 1). Confounding effects of anxiety and depression will be controlled by using the Hospital Anxiety and Depression Scale (HADS). In case of uncertainty concerning the mental state or possible active psychiatric disorders, the patient will first be evaluated by the psychiatric diagnosis team of the Antwerp University Hospital.

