**Fig. 2 Fig2:**
[figure not shown]
Schedule of enrolment, interventions, and assessments in accordance with the SPIRIT 2013 guidelines. tDCS transcranial direct current stimulation, TFI Tinnitus Functional Index, RBANS-H Repeatable Battery for the Assessment of Neuropsychological status adjusted for hearing-impaired individuals, CAEP cortical auditory evoked potentials

When patients are enrolled in the study, six sessions of sequential dual-site HD-tDCS (or sham stimulation for the control group) are planned within three weeks’ time (twice per week, with at least one day between sessions: T_a_ - T_f_). Stimulation (or sham) is provided for 30 min each session. The electrodes are positioned at the rDLPFC and the LTA. The positioning is according to the 10/20 international system for EEG electrode placement. For the rDLPFC stimulation, the central anode will be placed at F4 and the adjoining cathodes at F2, F6, FC4, and AF4 [24]. For the LTA stimulation, the central anode is positioned at CP5 with adjoining cathodes at C5, TP7, CP3, and P5. A constant current of 2 mA is applied for 15 min at each site with a fade-in and fade-out of 20s, resulting in a total stimulation duration of 30 min. For the sham stimulation, constant current will only be applied for 20s as previously described [30]. The direct current is transmitted by means of five sintered silver/silver chloride (Ag/AgCl) ring electrodes with inner radius of 6 mm and outer radius of 12 mm and delivered by a battery-driven Soterix Medical 1 × 1 tDCS low-intensity stimulator and 4 × 1 multichannel stimulation adaptor (Soterix Medical Inc., New York, NY, USA) with a maximum output of 2 mA. The ring electrodes are stabilized using HD-Electrode holders hooked in the Soterix Medical HD-cap and filled with EEG electrode gel (Neurax, Bonheiden, Belgium) following the guidelines for 4 × 1 HD tDCS stimulation [22].

Immediately after the last HD-tDCS session (T_f_), the patient is instructed to fill in all questionnaires. A follow-up (T_1_) at three months after the baseline measurements will contain the full clinical study protocol: pure tone audiometry, tinnitus analysis, SPIQ/SPIN, questionnaires, RBANS-H, and CAEP. A second follow-up (T_2_) is planned at six months after baseline measurements, comprising only the complete set of questionnaires.

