### Outcomes

#### Primary outcome measure

The primary outcome is the change in the Tinnitus Functional Index (TFI) questionnaire from baseline to follow-up at three months. The TFI is a self-reported questionnaire assessing the impact of tinnitus on quality of life [31, 32]. The patient must answer 25 questions on a Likert scale in the range of 0–10. For questions 1 and 3, which are expressed in percentages, the Likert scale is transformed to a 0–10 scale post hoc. The total score is then calculated as the mean of all questions multiplied by 10 and expressed as a number between 0 and 100. Results of the TFI include the total score and the score on eight subscales: intrusiveness; sense of control; cognition; sleep disturbance; auditory difficulties; relaxation; quality of life; and emotional distress. A decrease of 13 points on the total TFI score is considered as a clinically relevant difference [32]. Based on previous studies, we expect mean TFI scores at baseline of approximately 50 [28].

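### The exclusion criteria let patients with earlier tDCS or HD-tDCS enter, which puts patient blinding at risk on a self-rated primary outcome

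*Protocol article*

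**What the plan says.** Table 1 (Study setting) has a single criterion on earlier treatment, and it carries a time limit: "Patient having already had any other tinnitus treatment within the last two months". The Eligibility criteria section adds adult age and non-pulsatile tinnitus, but nothing on earlier neuromodulation. Recruitment is at a tertiary tinnitus clinic, and the Background states that "Clinical applications of tDCS and HD-tDCS include pain relief, especially in fibromyalgia, the treatment of major depressive disorder, and tinnitus".

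Under Interventions, "six sessions of sequential dual-site HD-tDCS (or sham stimulation for the control group) are planned within three weeks’ time". Active treatment is 2 mA for 15 min at each of two sites. In the other arm, "For the sham stimulation, constant current will only be applied for 20s as previously described". The same section names mild itching or tingling among the expected effects of active treatment.

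"The primary outcome is the change in the Tinnitus Functional Index (TFI) questionnaire from baseline to follow-up at three months", and the article describes the TFI as a self-reported questionnaire. The Blinding section keeps the patient blind up to and including the three-month visit. Allocation is stratified by TFI grade and gender. The primary model adjusts for age, gender, hearing loss, HADS score and TFI grade.

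**The concern.** A sham-controlled comparison on a self-rated score depends on patients not knowing their arm. A naive patient cannot compare 20 s of current with 15 min per site. A patient who has had the active procedure can. If sham is recognised, the expectation response in that arm may fall. If active treatment is recognised, the expectation response in that arm may rise. Both push the active-sham difference the same way.

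Randomisation spreads experienced patients evenly between arms in expectation, but it does not remove this bias, because recognition acts differently in each arm. Nothing in the stratification or the primary model refers to earlier stimulation. A covariate for it would in any case absorb only a shift common to both arms, not the arm-specific response.

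A lesser worry is carry-over: a patient may enter with a baseline TFI still lowered by an earlier course.

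**Working it through.** **1. Who can enter.** There are two readings of the Table 1 criterion.

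| Earlier tDCS or HD-tDCS | *other* = besides the course this trial gives | *other* = a different kind of treatment |
|---|---|---|
| More than two months ago | eligible | eligible |
| HD-tDCS within two months | excluded | eligible |

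The top row is the same on both readings. The bottom row depends on how a screener takes one word.

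**2. The plan's own sample size.** Inputs from Sample size and power: difference 13, SD 20, alpha 0.05 (taken as two-sided), power 80%.
- Normal approximation: n = 2 × 20² × (1.960 + 0.842)² / 13² = 37.2, so 38 per group.
- Two-sample t-test (noncentral t): 38.14, so 39 per group, as stated.
- Drop-out: 39 / 0.80 = 48.75, so 49. The plan recruits 50, which leaves 50 × 0.80 = 40 completers per group and a power of 81.9%.

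An added exclusion criterion changes none of these figures.

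**3. Recognition bias (illustration).** Let f be the share of experienced patients in each arm, and b the extra between-arm difference that recognition alone produces among them. Neither is in the article. Assumed ranges: f = 5% to 30%, b = 5 to 13 points.
- Bias d = f × b.
- SE = 20 × √(2/40) = 4.47.
- With no true effect, the two-sided rejection rate is 1 − Φ(1.96 − d/SE) + Φ(−1.96 − d/SE).

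| f | Bias, TFI points | Rejection rate at nominal 5% |
|---|---|---|
| 0% | 0 | 5% |
| 5% | 0.25 to 0.65 | 5.0% to 5.2% |
| 10% | 0.5 to 1.3 | 5.1% to 6.0% |
| 20% | 1.0 to 2.6 | 5.6% to 9.0% |
| 30% | 1.5 to 3.9 | 6.3% to 14.1% |

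**4. The opposite direction.** Experienced patients may instead gain less, for example because an earlier course did not help them. If they gain a fraction r of the 13 points, the mean difference is 13 × (1 − f) + 13 × r × f. At f = 10% this is 12.35 points for r = 0.5 and 11.7 for r = 0. Power with 40 completers per group then falls from 81.9% to 77.9% or 73.4%.

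**5. Time frame, for carry-over.** Two months is 8.7 weeks (61 days) and three months is 13.0 weeks. If sessions start at baseline and take three weeks, the primary endpoint falls about 13.0 − 3 = 10.0 weeks (70 days) after the last session. The look-back would then be 70 − 61 = 9 days shorter than the interval over which the trial tests its own effect. The article states no gap between baseline and first session, and a gap of about nine days would remove the difference.

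**The case against.** *The article is a condensed document.* Table 1 is not the whole eligibility text, since adult age and non-pulsatile tinnitus appear only in the prose, and the full protocol could hold a further criterion. That is possible. But Table 1 is presented as the trial's inclusion and exclusion criteria, and it fixes this rule and its time limit explicitly. The point concerns a stated rule, not an omitted detail.

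*Nothing shows that such patients exist here.* This stands as a limit on size. The article calls tDCS experimental and says that randomised trials in tinnitus are scarce. It also lists tinnitus as an existing application and recruits at a tertiary tinnitus clinic, so experienced patients are plausible but not counted.

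*Recognition and its direction are not established.* Active stimulation also has a 20 s fade-in and fade-out, the sham follows a cited method that is not shown, and returning patients may be earlier non-responders. The net sign is therefore uncertain. What stands is that the rule admits patients in whom blinding is less secure.

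Three stronger inferences are tempting and not supported:
- A reader might infer that earlier HD-tDCS is never excluded. That strains the word *other*, which more naturally means anything besides the treatment the trial gives.
- A reader might infer that carry-over biases the comparison. Randomisation balances it in expectation, so it mainly adds noise in both arms. Measuring at three and six months shows the persistence the trial looks for, not that an effect lasts that long.
- A reader might infer that the two-month look-back is shown to be too short. That rests on sessions starting at baseline. The six-month visit is a poor benchmark, because further treatment, including active HD-tDCS for sham patients, is allowed after three months.

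**Conclusion.** The point holds as a threat to patient blinding. On every reading of Table 1, a patient who had tDCS or HD-tDCS more than two months ago may enter; recent HD-tDCS is arguable. The outcome is self-rated, the sham is 20 s of current, and neither randomisation nor the planned model removes a recognition bias.

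The size cannot be derived from the article. It is nil if no experienced patient enrols and below one TFI point at an assumed 5% share. It reaches 1.5 to 3.9 points only at an assumed 30%. These figures show scale and are not estimates. Carry-over is a secondary matter of added noise. This is a worthwhile, inexpensive improvement to the eligibility criteria, not a flaw that invalidates the design.

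**What to change.** Make two edits to Table 1:
1. Add as an exclusion: *any previous tDCS or HD-tDCS*, without time limit.
2. In the two-month criterion, delete *other*, so that it covers any tinnitus treatment and all screeners apply it alike.

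The cost is one eligibility line and one screening question, with a small loss of eligible patients and a slightly narrower population. The sample size stays at 39 evaluable and 50 recruited per group. If the investigators prefer to admit experienced patients, a lighter and weaker alternative is to record prior exposure and each patient's guess of allocation, so that the effect of recognition can at least be examined. The treatment-free interval for other forms of neuromodulation is for the investigators to justify; the article gives no basis for a particular length.

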### Eligibility criteria

Adult patients (male/female) with chronic (> 6 months), non-pulsatile subjective tinnitus will be included in the study (Table 1). Confounding effects of anxiety and depression will be controlled by using the Hospital Anxiety and Depression Scale (HADS). In case of uncertainty concerning the mental state or possible active psychiatric disorders, the patient will first be evaluated by the psychiatric diagnosis team of the Antwerp University Hospital.

### Interventions

Participants are invited for a first clinical testing at the site (baseline measurement, T_0_). This testing consists of pure tone audiometry, psychoacoustic tinnitus analysis (loudness and pitch matching of the tinnitus), speech-in-quiet (SPIQ) and speech-in-noise (SPIN) measurements, questionnaires, and explorative research tests (Repeatable Battery for the Assessment of Neuropsychological Status, adjusted for hearing-impaired individuals [RBANS-H] and cortical auditory evoked potentials [CAEP]). The entire test protocol will take approximately 2.5–3 h. The schedule for patient visits and follow-ups is illustrated in Fig. 1. After the baseline measurements, patients are randomized into the HD-tDCS group or the sham control group. Figure 2 represents an overview of all interventions and outcome measures in accordance with the Standard Protocol Items: Recommendations for Interventional Trials (SPIRIT) 2013 guidelines [29] (Additional file 1).

**Fig. 1 Fig1:**
[figure not shown]
Visit and follow-up schedule. RBANS-H Repeatable Battery for the Assessment of Neuropsychological Status adjusted for hearing-impaired individuals, CAEP cortical auditory evoked potentials

**Fig. 2 Fig2:**
[figure not shown]
Schedule of enrolment, interventions, and assessments in accordance with the SPIRIT 2013 guidelines. tDCS transcranial direct current stimulation, TFI Tinnitus Functional Index, RBANS-H Repeatable Battery for the Assessment of Neuropsychological status adjusted for hearing-impaired individuals, CAEP cortical auditory evoked potentials

When patients are enrolled in the study, six sessions of sequential dual-site HD-tDCS (or sham stimulation for the control group) are planned within three weeks’ time (twice per week, with at least one day between sessions: T_a_ - T_f_). Stimulation (or sham) is provided for 30 min each session. The electrodes are positioned at the rDLPFC and the LTA. The positioning is according to the 10/20 international system for EEG electrode placement. For the rDLPFC stimulation, the central anode will be placed at F4 and the adjoining cathodes at F2, F6, FC4, and AF4 [24]. For the LTA stimulation, the central anode is positioned at CP5 with adjoining cathodes at C5, TP7, CP3, and P5. A constant current of 2 mA is applied for 15 min at each site with a fade-in and fade-out of 20s, resulting in a total stimulation duration of 30 min. For the sham stimulation, constant current will only be applied for 20s as previously described [30]. The direct current is transmitted by means of five sintered silver/silver chloride (Ag/AgCl) ring electrodes with inner radius of 6 mm and outer radius of 12 mm and delivered by a battery-driven Soterix Medical 1 × 1 tDCS low-intensity stimulator and 4 × 1 multichannel stimulation adaptor (Soterix Medical Inc., New York, NY, USA) with a maximum output of 2 mA. The ring electrodes are stabilized using HD-Electrode holders hooked in the Soterix Medical HD-cap and filled with EEG electrode gel (Neurax, Bonheiden, Belgium) following the guidelines for 4 × 1 HD tDCS stimulation [22].

Immediately after the last HD-tDCS session (T_f_), the patient is instructed to fill in all questionnaires. A follow-up (T_1_) at three months after the baseline measurements will contain the full clinical study protocol: pure tone audiometry, tinnitus analysis, SPIQ/SPIN, questionnaires, RBANS-H, and CAEP. A second follow-up (T_2_) is planned at six months after baseline measurements, comprising only the complete set of questionnaires.

Except for mild itching or tingling sensations, headaches, or fatigue, no adverse effects of HD-tDCS treatment are expected. In case patients do report serious side effects, HD-tDCS treatment will be discontinued.

No concomitant tinnitus treatment will be allowed between baseline measurement and the three-month follow up. After the three-month time point, participants will be allowed to undergo additional treatment. If participants were allocated to the sham group, they will have the right to undergo an actual HD-tDCS treatment free of cost after the three-month time point.

